### Cost-effectiveness analysis

The economic evaluation is embedded in the design of the clinical study and will be undertaken as a cost-effectiveness analysis with the costs per wetting incident avoided (over a 3 months period) as outcome measure. Based on available evidence it is supposed that the addition of the SENS-U device results in a dominant strategy. If so, no incremental cost-effectiveness ratio can be inferred and cost and effects will be reported separately. Additionally, a cost-utility analysis will be performed with the costs per quality adjusted life-year (QALY) as outcome. Analyses will be performed from a health care perspective (as base-case), and the time horizon is set at 6 months (to make inferences based on sustainability of effect). In case of confounding (baseline differences, etc.), the net monetary benefit approach (NMB) will be applied incorporating the confounders in the regression model with NMB as dependent variable or if dominance occurs the cost and effect outcome. Depending on the efficiency outcome, results will be displayed graphically by means of cost-effectiveness planes and acceptability curves. The Dutch guideline for economic evaluations will be adhered to (ZIN, 2016).

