### Urotherapy/bladder training

All subjects will receive urotherapy which starts with explanation and instructions. These instructions are also handed out in paper. At baseline, uroflowmetry and ultrasound to measure post void residual (PVR) is performed at least twice. Several patient-related outcome measurements (PROMS) are collected: a 48-h frequency voiding chart (FVC), questionnaires (Pediatric Incontinence Quality of Life (PINQ), EQ-5D-Y), and Rome IV criteria. Number and severity of wet days per week is assessed as baseline parameter.

After this, urotherapy is given for 12 consecutive weeks according to ICCS standards [6]. During this practice period, counseling is given at frequent follow-up appointments according to the local protocol in each center (at least two contact moments after intake and before follow-up at 3 months). Medication for constipation, prophylactic antibiotics, or medication to suppress bladder overactivity are continued if applicable. After 3 months of training, the urotherapist evaluates the outcome of training and number and severity of urinary incontinence per week is assessed again. Uroflowmetry and ultrasound for PVR and voiding diary/FVC parameters are collected again, and outcomes are discussed with the child and its parents. Questionnaires (PINQ, EQ-5D-Y) are filled in, and Rome IV criteria are determined.

If continence is not achieved (or not sufficiently) after 3 months, alternative treatments are discussed. Another contact moment is planned 6 months after start of the treatment to re-evaluate the status, assess the number and severity of urinary incontinence, and collection of previous mentioned PROMS. This is the end of the study period for participating subjects.

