### Randomization

Subjects are randomized to urotherapy for 3 consecutive months with or without 3 weeks use of SENS-U/SHAM device. Permuted block randomization with block size 6 stratified for age groups (6–7 years, 8–10 years, 11–15 years) will be done within each participating center by a computer. The program used is CASTOR EDC. Because some heterogeneity of urotherapy within the participating centers exists (in mode and interval of guidance by the urotherapist), the randomization will be performed within each center to correct for small differences between centers. Subjects are blinded for SENS-U versus SHAM device condition. An independent research member (other than the actual urotherapist treating the subject) is performing the randomization, assigns the device number (either SENS-U/SHAM) to the subject, plans the intake, and administers the device. This is done so outcomes can be attributed to the intervention itself and are only minimally influenced by behavior of the urotherapist who guides the training. The training period is 3 months with use of a device for 3 weeks if randomized to SHAM/ SENS-U during that period. Necessary unblinding during the period of device use (3 weeks) due to urgent medical reasons or unexpected serious adverse advents is very unlikely.

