### Data analysis and publication

Data are analyzed according to an intention to treat analysis, without replacement of individuals who withdraw during the study, using a Poisson or linear mixed model (depending on the distribution of the main outcome) with all available study time-points used. In case of premature withdrawal, last available data will be used. A correction for baseline, center, age, cumulative dose of antimuscarinics (if applicable), and adherence/drop-out will be performed. A random intercept and slope will be estimated if model fit allows for it. Descriptive statistics are used to analyze subjective improvement according to child and parents, adherence to treatment and to the SENS-U/SHAM device, user friendliness and (dis)comfort of the SENS-U/SHAM, and other previously mentioned outcome objectives. The data generated by the validated PIN-Q and EQ-5D-5L instruments are transformed and interpreted according to instructions given for each questionnaire [18–20]. A mixed model analysis is done to detect any difference in outcome between the three groups. Subgroup analysis will be done to study the effect of treatment in different age-groups, center, gender, socio-economic background, and in case of psychiatric co-morbidity. No interim analysis is done as no significant risks or benefits are expected for one of the three different study groups.

The results are shared with relevant fora and data will be presented at international conferences and published in peer reviewed medical journals without restrictions.

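### The economic analysis adjusts for covariates only if baseline differences are seen; adjustment should be fixed in advance, because the conditional rule loses precision and leaves room for discretion

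*Protocol article*

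**What the plan says.** All references are to the protocol article.

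- **Cost-effectiveness analysis.** The main economic measure is cost per wetting incident avoided over 3 months. In addition, "a cost-utility analysis will be performed with the costs per quality adjusted life-year (QALY) as outcome", and "the time horizon is set at 6 months". On covariates the section says: "In case of confounding (baseline differences, etc.), the net monetary benefit approach (NMB) will be applied incorporating the confounders in the regression model". If one strategy dominates, the same adjustment moves to the cost and effect outcomes. No criterion for confounding is given.
- **Data analysis and publication.** For the clinical mixed model there is no condition: "A correction for baseline, center, age, cumulative dose of antimuscarinics (if applicable), and adherence/drop-out will be performed".
- **Randomization.** Permuted blocks, stratified by age group, are used in each centre, and "the randomization will be performed within each center to correct for small differences between centers".
- **Urotherapy/bladder training.** The baseline measurements include "questionnaires (Pediatric Incontinence Quality of Life (PINQ), EQ-5D-Y), and Rome IV criteria". At 3 months, "Questionnaires (PINQ, EQ-5D-Y) are filled in, and Rome IV criteria are determined". The 6-month contact is to "assess the number and severity of urinary incontinence, and collection of previous mentioned PROMS".

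**The concern.** In a randomised trial a baseline difference between arms is chance, not confounding in the usual sense. A covariate earns its place in the model because it predicts the outcome or was used to randomise. Whether it happens to be unbalanced in this sample is not the reason. The economic section makes the observed imbalance the reason, and it does not say how large an imbalance must be or which variables count.

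Three things are at stake:

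- When nothing triggers adjustment, the precision that baseline values would give is lost.
- An imbalance too small to trigger adjustment stays in the estimate.
- The analyst decides after seeing the data whether to adjust and for what.

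This matters here because the Aim and objective section makes cost-effectiveness the aim of the study. The economic analysis nevertheless has a weaker rule than the clinical one.

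**Working it through.** **The plan's own figures.** The article gives no sample size or precision figure for the economic analysis. Its clinical figure of 124 per group reproduces (64% against 79%, one-sided 0.05, 80% power, continuity-corrected; exact Fisher power at 124 is 0.806). The percentages below do not depend on the number of children.

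**Inputs.** From the article: EQ-5D-Y at months 0, 3 and 6, and a 6-month horizon. Assumed, because the article does not give them: QALYs as area under the utility curve, equal SD at the three visits, and an equal correlation *r* between any two visits, with range 0.3 to 0.7.

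**Step 1: weight of baseline utility in the QALY.** The trapezoid rule over two intervals of 0.25 year gives weights of 0.125, 0.25 and 0.125 on months 0, 3 and 6. In units of the utility variance:

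- covariance of QALY with baseline utility = 0.125 + 0.375*r*
- variance of QALY = 0.09375 + 0.15625*r*
- R² = (0.125 + 0.375*r*)² / (0.09375 + 0.15625*r*)

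**Step 2: always adjusting against never adjusting.** The standard error is multiplied by √(1 − R²).

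| *r* | R² | √(1 − R²) | SE cut |
|---|---|---|---|
| 0.3 | 0.2375²/0.1406 = 0.40 | 0.774 | 23% |
| 0.5 | 0.3125²/0.1719 = 0.57 | 0.657 | 34% |
| 0.7 | 0.3875²/0.2031 = 0.74 | 0.511 | 49% |

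**Step 3: the conditional rule.** The article states no trigger. As an illustration only, suppose adjustment happens when the baseline difference has p < 0.05. About 5% of trials would then adjust. A simulation of 200,000 runs with 124 per arm, for an outcome with correlation ρ to its own baseline value, gave:

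| ρ | Relative variance, always | Relative variance, conditional | Two-sided type I error, conditional |
|---|---|---|---|
| 0.3 | 0.91 | 0.97 | 0.047 |
| 0.5 | 0.75 | 0.93 | 0.043 |
| 0.7 | 0.51 | 0.86 | 0.036 |

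The conditional column follows 1 − 0.279ρ². The untriggered part of a standard normal difference keeps 0.95 − 2 × 1.96 × 0.0584 = 0.721 of its variance, so 0.279 is removed.

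For the QALY, put the R² of step 2 in place of ρ². The conditional relative variance is then 0.89, 0.84 and 0.79. Always adjusting cuts the standard error, compared with this rule, by 1 − √(0.599/0.888) = 18%, 1 − √(0.432/0.841) = 28% and 1 − √(0.261/0.794) = 43%. A looser trigger would leave a smaller gain.

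**Step 4: imbalance that does not trigger.** A baseline difference of 1.5 standard errors is below the illustrative trigger. Left unadjusted, it shifts the estimate by 1.5ρ standard errors of the outcome difference: 0.45, 0.75 and 1.05 for ρ = 0.3, 0.5 and 0.7.

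**Step 5: net monetary benefit.** Net benefit is the valued QALY minus cost. If baseline utility explains little of the cost, its R² for net benefit is roughly the QALY R² times the share of net-benefit variance that comes from QALYs. The article gives no cost variance, so the gain cannot be put in figures beyond being smaller than in step 2.

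**The case against.** The strongest case against the point has five parts.

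1. *The rule does adjust for imbalance that is noticed.* This stands. A reader might infer that a chance difference in baseline utility passes unchecked into the QALY difference. That would describe a plan that never adjusts, whereas this one names baseline differences as the trigger. Only imbalance that fails to trigger stays in.
2. *Data-driven does not mean invalid.* This stands. A reader might infer a raised false-positive rate. Under the illustrative trigger the type I error was 0.036 to 0.047, which is conservative.
3. *The QALY analysis is the additional one.* This stands. The 23% to 49% concerns QALYs and is relative to never adjusting. It cannot be read as the gain for the cost-effectiveness result as a whole. For the main economic measure the matching covariate is the baseline wetting count, not utility.
4. *The clinical effect on wetting accidents is already adjusted.* This is true for the mixed model and narrows the gap, but that model does not cover costs, QALYs or net benefit.
5. *A covariate list may sit in an economic analysis plan that is not shown, and the sentence does not say that adjustment happens only then.* An absent list is indeed no fault of an article. The article does state a condition, however, and a later plan that followed it would inherit it.

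**Conclusion.** The point holds as one of efficiency and prespecification, not of validity. The article ties regression adjustment in the economic analysis to observed baseline differences. It does so although allocation is randomised, the strata are known in advance, baseline utility is collected, and the clinical model adjusts without condition.

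The size rests on assumptions. With area-under-the-curve QALYs, equal SDs and an equal between-visit correlation of 0.3 to 0.7, always adjusting for baseline utility cuts the standard error of the QALY difference by about 23% to 49% against never adjusting. Against the conditional rule the gain is smaller and depends on the unstated trigger; it is 18% to 43% under the illustrative p < 0.05 trigger. For net monetary benefit it is smaller still by an unknown amount, and for wetting incidents and costs no figure is derived here. The documents do not support a claim of inflated type I error or of imbalance that always goes uncorrected.

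**What to change.** In the Cost-effectiveness analysis section, delete the opening condition about confounding and baseline differences. State instead that incremental costs, effects and net monetary benefit are always estimated by regression on arm, centre and age stratum, whatever the observed balance, with these additions:

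- baseline EQ-5D-Y utility for QALYs and for QALY-based net benefit;
- baseline wetting accidents per week for wetting incidents avoided, using the same baseline measure as the clinical model.

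The cost is one sentence. The baseline values and the stratification factors are already in the trial's data, so no new data are needed. If a separate economic analysis plan exists, it should carry the same sentence.

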## Discussion

To our knowledge, this is the first trial studying cost-effectiveness of urotherapy and more specifically alarm interventions added. Given the overall prevalence of LUTD, a yearly amount of approximately 8600 children with functional DUI are referred for treatment in the Netherland each year (data retrieved from Statistics Netherlands). Urotherapy as the first treatment of choice is not always sufficient [7]. Additional treatments include medication (mainly off-label or with unwanted side effects), surgery to exclude and treat any type of anatomical anomaly, botulinum toxin, or neuromodulation. Most of these treatment options are either time consuming, expensive, require general anesthesia, or are associated with undesired side effects without the certainty of a successful outcome. As treatment of incontinence is lengthy and therefore difficult to sustain for both children and parents, there is room for improvement of current urotherapy, being the cornerstone of LUTD treatment, because incontinence is a burdensome disease which negatively influences quality of life and self-confidence in children [4]. The SENS-U might help in this process. For professionals, the SENS-U can easily provide data on bladder filling and incontinence during the training and help them to give adequate feedback to the children. For children, the SENS-U can help in the interpretation of the sensation of a full bladder, with subsequent voiding and less urinary incontinence.

If the SENS-U is added to urotherapy, an initial higher complete response of training is expected. An increased number of children is cured in a shorter period of time with less need for other expensive, invasive, and/or time consuming treatments. Furthermore, the possible psychological stress associated with complex medical treatment (like surgery) is prevented.

This study has several strengths. Children from first-, second-, and third-line centers throughout several areas in the Netherlands are included to represent the overall group of children with functional DUI as much as possible. It is one of the few studies that will give a better insight in adherence of alarm systems used, as current literature concerning this element is sparse. As previously mentioned, trials studying not only the effect but also the cost-effectiveness of certain treatment modalities are essential as overall health costs are increasing. The study also has some potential limitations. Complete blinding of subjects is only possible for those allocated to either a SENS-U or SHAM device. Those allocated to urotherapy alone are not blinded (nor is the urotherapist in this case). As cognitive behavioral treatment is an important part of training, motivation in those not randomized to any type of device might be impaired. Potential discomfort or social embarrassment in those allocated to a SENS-U or SHAM might lead to less adherence and subsequent impact on outcome as well.

## Trial status

At the moment, all study centers are finalizing the required procedures to start inclusion. The first patients are included in March 2022. Patient recruitment is planned to be complete in 2024.

## Data Availability

At the end of the study, all generated (meta)data will be stored as a proprietary format in a secured data archive called DANS EASY (https:// easy.dans.knaw.nl). In addition, metadata of published collections can be found through Narcis (https://www.narcis.nl/). Data will be available on request. In line with privacy legislation, it is required that users of these data can be identified (e.g., in case of violation of Data Use Agreement). Therefore, potentially identifiable data are shared under a specific data Use Agreement that requires authentication to download these data sets.
